### Physical therapists in the participating clinics

All patients will be treated by PTs in the participating clinics. In each clinic, at least one PT will be instructed about the classification system, and at least one PT will be instructed about the usual care procedure, depending on preference and expertise. PTs who will provide manipulation treatment must be licensed, post-graduate MTs or in the 4^th ^and final year of the MT master education program at the Educational Center for Musculoskeletal Therapies (SOMT) in the Netherlands. No extra qualifications will be required to treat patients according to the classifications of direction-specific exercises and stabilisation. The number of years of experience of the PTs, and their post-graduate education in MT and/or MDT, will be recorded for both treatment groups. To minimise contamination, the PTs who will provide the classification-based treatment will not be allowed to provide usual care, and vice versa.

The PTs who will provide the classification-based treatment will follow a five-hour training session in which the treatment protocols will be described and discussed. Experts on direction-specific exercises ([name]) and stabilisation will provide the training. The PTs will receive a detailed manual of the study, and a translation of the registration forms and treatment protocols used in the Brennan et al. study [18]. The PTs providing usual care will receive a two-hour training course in the rationale and treatment components described in the LBP guidelines issued by the Royal Dutch College for Physical Therapy (KNGF) [27,28].

### Intervention according to the Dutch LBP guidelines

Patients assigned to usual care will receive PT or MT according to the current Dutch LBP guidelines [27,28]. The PTs providing usual care will not be informed about the physical examination and classification procedure, and will therefore reassess the patient to obtain the relevant information for treatment. However, to avoid inconvenience for the patient, and to increase the chance that the patient remains unaware of the treatment allocation, the PT will receive a written description of the patient's medical history from the research PTs. The patients will receive supervised, individually tailored treatment based on their clinical presentation. Treatment techniques vary within and among PTs, and depend on the preferences and expertise of the PTs. The focus of the treatment will be on improving function and participation. Interventions that are commonly used in Dutch primary care are 'hands-on' muscular mobilisation techniques, specific articular mobilisation and manipulation techniques, strength and stability exercises, massage, and cognitive, respondent and operant techniques, such as relaxation exercises and graded activity programmes. Decisions about the frequency and the number of sessions are left to the discretion of the PT. The number of treatment sessions, the treatment modalities, the treatment goals, any deviations from the protocol, and reasons for prematurely terminating treatment, will be recorded.

### Interventions according to the classification system

Before providing any treatment, the PTs in this group will be informed about the results of the classification procedure. Patients will receive either direction-specific exercises, spinal manipulation, or stabilisation.

#### I. Direction-specific exercises

Patients will perform exercises in the direction that matches their directional preference: extension, flexion, lateral (side-gliding right or left) or flexion-rotation (right or left). For each direction is a treatment protocol which contains patient-generated forces (sustained positions and/or repeated movements) and PT-generated forces (mobilisations in the direction of preference). The protocol can be adapted to the patient's pain responses. All patients will receive a booklet containing information about directional preference and centralisation, the exercises, and the correct performance and frequency of each exercise. The patients will be instructed to perform the exercises four times a day, to correct their posture in the preferred direction, and to avoid activities and positions that increase the intensity or peripheralisation of symptoms. The patients will also be asked to keep an exercise logbook to monitor their compliance.

#### II. Spinal manipulation

Patients will be treated with high velocity thrusts directed at the spinal levels from T12 to L5 and/or the sacroiliac region. Decisions about the choice of the technique (long lever to manipulate multiple levels or short lever to manipulate one specific level) and the location of the forces are left to the discretion of the PTs. The most common spinal manipulation technique in the Netherlands is one of the two technique options in the Brennan et al. study [18], with the patient lying on his/her side. The symptomatic side is manipulated first. If the patient cannot specify a symptomatic side, the PT can select a side. During each session, the PT can make a maximum of four attempts (two on each side) to achieve a cavitation (i.e. 'a pop') heard or felt by the PT or the patient. Each session will end with 10 active flexion and extension movements of the lumbar spine in a supine or quadruped position within the limits of pain. The choice of this flexion-extension exercise will be made by the PT. Patients will be instructed to perform this active exercise once a day. The PT will record the number of attempts, whether or not a cavitation is heard or felt, and the technique that is used (long or short lever). The PT is allowed to provide spinal manipulation treatment for a maximum of 6 sessions.

#### III. Stabilisation

First, the patients will be taught to activate their local stability system to control neutral joint position in a supine position [29]. This (slight) co-activation of the lumbar multifidus with the transversus abdominus ('drawing in' the stomach) must be accompanied by minimal trunk movements and relaxation of global muscles such as the upper abdominal muscles. The patients will then be instructed to perform these abdominal bracing exercises ('drawing in' the stomach with normal breathing) during strengthening exercises in standing, quadruped, and side-support positions. Apart from these standardised exercises, activity of the local and global muscle systems will be trained in positions and movements that aggravate the patient's pain, in order to restore functional capacity and to improve dynamic control. The patients will also receive an instruction booklet, and will be instructed to perform the exercises once a day and to keep self-monitoring exercise diaries.

For all classification-based interventions, the treatment frequency, amount and type of exercises, and the duration and progression of the programme will be recorded, and directed by the judgment of the PT. The treatment frequency will only be restricted for spinal manipulation (maximum of 6 sessions). The patients will be treated according to their primary classification for a minimum of 4 weeks, during which the PT will be allowed to change the treatment strategy, if (1) the functionality of the patient improves significantly (a reduction of >30% on the ODI, compared to the score at baseline) or (2) the symptoms are severely aggravated. After the first 4 weeks, the PT will be allowed to provide follow-up interventions. At the end of each patient's treatment period, the PT will note the degree of satisfaction with the classification-based treatment, measured on a 5-point Likert scale ranging from very satisfied to very dissatisfied.

In both treatment groups, the patients are requested not to receive any co-interventions apart from the physical therapy (such as complementary and/or alternative medicine [CAM]) during the intervention period. All patients will be asked to stay active, and to engage in general exercise activities (e.g. a sports club). The principal investigator will regularly monitor the PTs for compliance with the treatment protocols, by means of visits, phone calls and e-mail contact.

### Blinding

The PTs will be asked not to disclose the treatment allocation to the patients, and the success of the blinding will be evaluated at the 8-week follow-up. The research assistants and the participating statistician will be blinded for the patient's group assignment. The research PTs and the treating PTs cannot be blinded for the treatment allocation, but they will not be involved in the outcome date-collection.

### Measurements

The baseline questionnaire will include questions about socio-demographic characteristics (e.g. age, gender, marital status, etc.) and all primary and secondary outcome measures.

### Primary outcome measures

Global perceived recovery will be measured by self-assessment on a 7-point Likert scale ranging from "completely recovered" to "worse than ever" [30]. This will be dichotomised into success (complete and much recovered) and non-success (slightly recovered, no change, slightly worse, much worse and worse than ever). This measure has been found to be useful in LBP research [31].

Functional status will be measured according to the Dutch translation of the ODI, version 2.1a [32,33]. The ODI is sub-divided into 10 sections related to activities of daily living. Each section consists of 6 graded responses, scored 0-5, and the total score can range from 0 (no difficulty at all) to 50 (maximal difficulty). The ODI is widely used in LBP studies, and has also been used as a primary outcome measure in studies focusing on the treatment-based classification approach [12,18].

Pain intensity over the previous week will be measured on an 11-point numerical rating scale (0 = no pain to 10 = worst imaginable pain), with reliability, validity, and sensibility to change that are commonly accepted in LBP research [34-36].

### Secondary outcome measures

General health status will be evaluated with the Short Form 36 (SF-36) [37]. It consists of 36 questions that can be aggregated to form eight sub-scales (physical functioning, mental health, general health perceptions, pain, role limitations physical, role limitations emotional, social functioning, and vitality) and two sum-scales (physical and mental component scales). The scores on all sub-scales range from 0-100, with higher scores indicating better outcomes. It is a widely used measurement instrument with satisfactory validity, reproducibility and responsiveness to change [38], and the Dutch translation has been found to be sufficiently valid [39].

Health-related quality of life will be measured with the EuroQol (EQ-5D) [40]. This questionnaire assesses 5 dimensions (mobility, self-care, usual activities, pain/discomfort and anxiety/depression) on a 3-point scale; no problems, moderate problems and severe problems. The questionnaire is appropriate for estimating quality-adjusted life-years (QALYs), and can be used for cost-utility analysis. The total score is expressed in utilities according to the Dolan model [41]. The questionnaire has been found to have adequate psychometric properties, and is commonly used in LBP research [42]. QALYs will be calculated by multiplying the utility of a health state by the time spent in this health state, based on the Dutch valuation tariff [43].

Fear-avoidance beliefs will be measured with the Dutch version of the Fear-Avoidance Beliefs Questionnaire (FABQ) [44]. It consists of two multi-item scales, measuring the patient's beliefs about how physical activity (FABQPA, 5 questions) and work (FABQW, 11 questions) affect their LBP. Following the recommendations of Waddell et al. [44], only 4 items will be included to score the FABQPA sub-scale (range 0-24) and 7 items to score the FABQW sub-scale (range 0-42). Higher scores indicate more fear-avoidance beliefs.

Psychosocial status will be measured with the Örebro Musculoskeletal Pain Screening Questionnaire (ÖMPSQ) [45]. This questionnaire contains 25 items, divided into five groups (function, pain, psychological factors, fear-avoidance, and miscellaneous), 21 of which are scored on a 0-10 scale. The scores of the items are summed to provide a total score range of 0-210, with higher scores indicating a higher risk of a poor outcome. The ÖMSPQ has been found to be a reliable and valid predictor of outcome for patients with acute, subacute and chronic LBP [46,47].

Work absenteeism and presenteeism will be measured with the Productivity and Disease Questionnaire (PRODISQ) [48]. This questionnaire was developed and validated in samples of patients and workers in the Netherlands, and covers all relevant aspects of the relationship between health and productivity.

Direct and indirect costs will be measured by means of self-completed cost diaries [49]. The following costs will be evaluated: i) health care costs (e.g. primary care, medical specialist care, prescription of medication, professional home care and hospitalisation); ii) patient and family costs (out-of-pocket expenses, such as over-the-counter medication and the costs of paid and unpaid help); and iii) costs of loss of productivity (work absenteeism and presenteeism, and costs due to days of inactivity for patients without a paid job).

Table 1 presents an overview of the data-collection procedures.

**Table 1 T1:** Overview of the data-collection

Instrument	Baseline	8 weeks	26 weeks	39 weeks	52 weeks
Demographic data	X				
Physical characteristics and primary classification	X				
					
*Primary outcome*					
Global perceived recovery		X	X		X
Disability (ODI)	X	X	X		X
Pain intensity (NRS)	X	X	X		X
					
*Secondary outcome*					
General health (SF-36)	X	X	X		X
Health-related quality of life (EQ-5D)	X	X	X		X
Fear-avoidance beliefs (FABQ)	X				X
Psychosocial status (ÖMPSQ)	X				X
					
*Economic evaluation*					
Costs (PRODISQ and cost diary)		X	X	X	X

Abbreviations: ODI = Oswestry Disability Index, NRS = Numerical Rating Scale, SF-36 = Short Form 36, EQ-5D = EuroQol, FABQ = Fear-Avoidance Beliefs Questionnaire, ÖMPSQ = Örebro Musculoskeletal Pain Screening Questionnaire, PRODISQ = PROductivity and DISease Questionnaire

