### Data-analysis

Baseline characteristics of the two intervention groups with regard to the most important prognostic indicators and main outcome measures will be compared to assess the adequacy of the randomisation. If necessary, adjustments will be made for baseline characteristics. The primary analysis will be an intention-to-treat analysis. A per protocol analysis will be performed to estimate the extent to which protocol deviations might have biased the results. The data will be analysed in a linear mixed model, with responses at 0 (baseline), 8, 26 and 52 weeks. In this model, the effect of interest is the time × treatment interaction. Estimates of treatment effects, with 95% confidence intervals between baseline and follow-up measurements, will be calculated and compared between the two treatment groups. Multivariable regression analysis will be used to adjust for possible baseline differences, and multilevel analysis will be performed, with PT, patient, and time of measurement as levels. Additionally, as a secondary analysis, a responder analysis will be performed according to the cut-off values as proposed by a consensus panel [50]. If there are many missing data, the missing data will be imputed with multiple imputation techniques.

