### Economic evaluation from a societal perspective

The cost-effectiveness analysis will be carried out from a societal perspective. The total back-pain-related costs for patients in both intervention groups will be compared with the health effects of the two groups, and cost-effectiveness ratios will be calculated for the primary outcome measures. The economic evaluation will be performed according to the intention-to-treat principle. Costs will be valued according to the guidelines published in the updated handbook for economic evaluation in the Netherlands [51]. The costs of production losses due to LBP will be estimated for both paid and unpaid labour [52]. For paid labour, the costs will be calculated, using both the human capital approach and the friction cost approach. For unpaid labour, the indirect costs will be estimated as the costs of production losses due to LBP, e.g. voluntary work and household work, based on shadow prices. The costs will be summed for each individual patient, and bootstrapping will be used to make a pair-wise comparison of the mean differences in total costs between the two groups. Confidence intervals will be obtained by bias-corrected and accelerated bootstrapping, using 2000 replications [53].

Cost-utility and cost-effectiveness ratios will be estimated, using bootstrapping techniques. The differences in costs will be compared, and related to the differences in effects (global perceived recovery, functional status and pain intensity) and differences in QALYs. Bootstrapped cost-effect pairs will be used to estimate cost-effectiveness planes and cost-effectiveness acceptability curves. Cost-effectiveness acceptability curves indicate the probability that a treatment is cost-effective at a specific ceiling ratio, which is the amount of money society is willing to pay to gain one extra unit of effect. Sensitivity analysis will be performed on the most important cost-drivers, in order to assess the robustness of the results.

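### The protocol names two scoring sources for the EQ-5D, one for utilities and another for QALYs, without saying how they relate; baseline utility could also be prespecified as a QALY covariate at no cost

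*Protocol article*

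**What the plan says.** In the protocol article, Secondary outcome measures, the EQ-5D paragraph makes two statements about scoring. On the utility: "The total score is expressed in utilities according to the" model of reference 41. On the QALY: it is the utility multiplied by the time for which it applies, "based on the Dutch valuation tariff" of reference 43.

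Table 1 schedules the EQ-5D at baseline and at 8, 26 and 52 weeks.

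The section on the economic evaluation uses bootstrapping. Cost differences are to be "related to the differences in effects (global perceived recovery, functional status and pain intensity) and differences in QALYs". It values costs by the Dutch handbook for economic evaluation and does not mention baseline utility.

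The Data-analysis section has two general statements on baseline adjustment: "If necessary, adjustments will be made for baseline characteristics", and "Multivariable regression analysis will be used to adjust for possible baseline differences". Neither names QALYs.

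**The concern.** A value set turns the five EQ-5D answers into one utility. The paragraph names one source for that step and, when it comes to QALYs, names another. The only utility defined up to that point is the one from reference 41, so the QALY sentence appears to take that utility and attribute it to a different tariff. If two value sets are used, a reader could not rebuild the QALYs from the utilities reported as a secondary outcome. While the choice is open, it could also be settled after the data are seen.

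The second issue is smaller. A QALY over 52 weeks includes the baseline utility and is correlated with it. If adjustment depends on whether an imbalance is observed, the estimator of incremental QALYs is not fixed in advance, although the covariate will be available for use.

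At stake is the cost-utility part of the economic evaluation: the QALY-based ratio, its plane and its acceptability curve.

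**Working it through.** **Part 1: the value set.** The document gives no utility, QALY or tariff figure, so there is nothing to reproduce. The two statements can be reconciled in three ways:

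| Reading | Consequence for the text |
|---|---|
| Utilities from reference 41 feed the QALYs | The Dutch-tariff clause is wrong |
| Reference 41 scores the secondary outcome; the Dutch tariff scores the QALYs | Two utility scales may appear in one report, and this should be said |
| Reference 41 names only the form of the scoring model, and the Dutch weights are used throughout | The utility sentence does not say which weights apply |

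Each reading needs a correction or a clarifying sentence. The document does not choose between them. How far utilities would differ between the two sources cannot be calculated, because neither set of weights is shown.

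**Part 2: the scale of the gain from baseline adjustment.**

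Inputs from the document:
- EQ-5D at 0, 8, 26 and 52 weeks (Table 1).
- 75 patients per group (Sample size).

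Assumptions not in the document:
- QALYs by the trapezoid rule.
- The same utility SD at every visit, 0.20 to 0.25.
- The same correlation r between any two visits, 0.3 to 0.5.

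1. Trapezoid weights for 0, 8, 26 and 52 weeks: 4/52, 13/52, 22/52 and 13/52, that is 0.077, 0.250, 0.423 and 0.250.
2. Slope of the QALY on baseline utility = 4/52 + r × 48/52.
   - r = 0.3: 0.077 + 0.277 = 0.354.
   - r = 0.5: 0.077 + 0.462 = 0.538.
3. Variance of the QALY in units of SD² = r + (1 − r) × Σw², with Σw² = (16 + 169 + 484 + 169)/2704 = 0.310.
   - r = 0.3: 0.3 + 0.7 × 0.310 = 0.517.
   - r = 0.5: 0.5 + 0.5 × 0.310 = 0.655.
4. Share of QALY variance explained by baseline = slope²/variance.
   - r = 0.3: 0.125/0.517 = 0.24.
   - r = 0.5: 0.290/0.655 = 0.44.
5. Effect on the standard error of incremental QALYs = √(1 − R²): √0.76 = 0.87 and √0.56 = 0.75. The standard error falls by about 13% to 25%.
6. Standard error of a chance baseline difference = SD × √(2/75): 0.20 × 0.163 = 0.033 and 0.25 × 0.163 = 0.041.
7. Movement of an unadjusted QALY difference for a one-standard-error baseline difference: 0.354 × 0.033 = 0.012 at the low end and 0.538 × 0.041 = 0.022 at the high end.

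With wider assumptions (SD 0.15 to 0.30, follow-up-on-baseline slope 0.3 to 0.7), step 7 gives 0.009 to 0.035. If baseline did not predict later utility at all, only the 4/52 weight would act and the movement would be 0.002 to 0.004.

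**The case against.** **On the value set.** A reader might infer that the cost-utility result itself mixes two value sets. The document does not establish this. The only tariff named for QALYs is the Dutch one, and on a plain reading it may be used for them throughout. It is also possible that reference 41 denotes only a form of model. What stands is that the text names two sources and leaves the reader to guess, which a clarifying sentence would resolve.

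**On baseline utility.** A reader might infer that QALY differences will be left unadjusted, and that the result then depends on baseline luck. No sentence says so. Bootstrapping does not exclude covariates, and the Data-analysis section provides for baseline adjustment in general. The covariates of a QALY model are also something a journal article commonly leaves to the full protocol or analysis plan, so silence here is not an error.

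Nor would an unadjusted comparison be biased. Under randomisation a chance imbalance is noise, and an unadjusted bootstrap interval already contains it. The calculation also treats allocation as simple randomisation. The trial stratifies on complaint duration and on ODI below or at least 25%, in blocks of four. To the extent that utility tracks disability, imbalance will be smaller than shown, and so will the extra precision from baseline utility beyond those factors. These objections stand, and for that reason this part is offered as an improvement and not as a defect.

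**On scope.** The economic evaluation relates costs to four effect measures. Recovery, ODI and pain do not use the EQ-5D.

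**Conclusion.** The EQ-5D scoring is stated inconsistently within one paragraph and should be corrected. The secondary outcome and the QALYs may rest on different value sets; whether they do, and by how much results would differ, cannot be determined from the document.

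Prespecifying baseline utility as a covariate is worthwhile but secondary. Its benefit is precision and removal of conditional imbalance: about 24% to 44% of QALY variance, or a standard error smaller by roughly 13% to 25%. These figures rest on the assumed trapezoid rule, equal SDs and an exchangeable correlation of 0.3 to 0.5. The shift of 0.012 to 0.022 QALYs per standard error of imbalance rests in addition on an assumed SD of 0.20 to 0.25, 75 per group and simple randomisation.

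The consequence is confined to the EQ-5D secondary outcome and the QALY-based cost-utility analysis.

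**What to change.** 1. In the EQ-5D paragraph, state that the Dutch tariff of reference 43 gives both the utilities reported as a secondary outcome and the QALYs. It is already the tariff named for QALYs, and it matches the Dutch valuation of costs. If the model of reference 41 is kept as a second value set, label it a sensitivity analysis.
2. In the economic evaluation, state that incremental QALYs are estimated within each bootstrap replicate by regression on arm, baseline EQ-5D utility and the two stratification factors (complaint duration and ODI category), whether or not an imbalance is observed.

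The first change is wording only. The second adds a sentence and covariates to the bootstrap code. Neither needs new data, because EQ-5D and the stratification factors are recorded at baseline.
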